### Sample size

There is little published literature about the likely design effect size in healthcare interventions and hayfever quality of life, however using data from a previous parallel group study using the RQLQ in adults with perennial rhinitis [17], a mixed-model analysis of variance gave an F-ratio of less than unity, indicating that there was less variation between practices than would be expected by chance (data available on request). This means that the inter-practice variance and hence the ICC is estimated as zero, and there would thus be no anticipated design effect for the proposed cluster randomised trial. There are however obvious differences between the study in adults and this cluster trial in adolescents, including the trial design; estimates of the between-practice variation in the proposed study and its effect on sample size are shown in Table 1.

**Table 1 T1:** Number of patients needed with varying ICCs

ICC	Cluster size	No. of clusters	No. of patients
0.01	10	20	200

0.02	10	22	220

0.05	10	24	240

Sampsize [21] was used for sample size calculations. A cluster size of 10 was chosen as pilot work suggested that it should be possible to recruit at least this number of adolescents with diagnosed current hayfever from most general practices (data available on request).

Taking account of the cluster design, using a standard deviation of 1.2 [20] with a power of 80% to detect a minimal clinically important difference of 0.5 in RQLQ(S) score at a significance level of 5%, an estimate of the cluster size of 10 and an ICC of 0.02 required a total of 22 clusters and an adjusted sample size of 220 patients (unadjusted 180).

Based on these figures, we aimed to recruit at least 22 practices, inflated by 20% to account for possible losses to follow-up, resulting in 22 clusters (practices) recruiting 12 patients per practice, giving a total of 264 patients in the study (i.e. 132 per arm).

With these numbers, the study is sufficiently powered for the primary outcome measure; it is however likely to be underpowered for the secondary educational outcomes based on examination data [13].

### Compliance

All practices were given clear written information on what the study involved and were visited by the researcher prior to agreeing to take part in the study. In order to maximise the opportunities for intervention HCPs to attend the training, the course was run twice on separate dates in two different venues; all intervention HCPs attended a training day. The researcher assisted the practice with the mailings and reminders to eligible patients, and a clear account of payment for all practice time was given to the practices at the beginning, which included administrative time and backfill for the HCPs attending the training. The control group practices were offered the same short course at the end of the study and this was attended by nine out of the 12 control practices.

### Withdrawal of patients from the study

There were three points at which consenting patients could withdraw from the study:

i) prior to completing baseline questionnaires

ii) prior to attending the practice nurse appointment

iii) prior to completing the six weeks post-intervention questionnaires.

### Statistical analysis

Data analysis, using the following analysis plan, will be undertaken blind to the allocation arm. The primary analysis will be a per protocol analysis on complete cases only. An intention-to-treat analysis using the last observation carried forward is not feasible since imputing of the baseline data (which were collected before the pollen season) for subjects whose final RQLQ(S) is missing would not be a conservative assumption. This is because the lack of change from a value measured before the hayfever season might be better than expected. (i.e. baseline values may be low on a scale of 0-6 where 0 is not troubled and 6 is extremely troubled, and imputing these data for an RQLQ measured at the peak of the season, which may have been high might result in over-estimation of the intervention effect if more cases had missing data in the intervention group.)

### Descriptive analyses

#### Describing baseline characteristics of patients and practices

a) For each treatment arm, we will describe:

i) Patient age (mean and SD) and sex (number and percentage)

ii) Practice list size (median and IQR, or mean and SD if normally distributed)

iii) Practice population by age group (number and percentage)

iv) Practice deprivation (IMD or proxy measure)

v) Whole time equivalent GPs and practice nurses per practice (median and IQR, or mean and SD if normally distributed).

#### Comparison between treatment arms

The difference in the validated RQLQ(S) score between the intervention and control groups at baseline and six weeks post-intervention will be compared.

#### Adjusting for

1. Practice level stratum (region, list size and IMD or proxy) and baseline RQLQ(S).

2. Practice level stratum (region, list size and IMD or proxy). This will potentially be a more powerful comparison in the event that substantial numbers of subjects provide follow-up data, but not baseline data.

Multi-level modelling using a random-effects model will be used to take account of between and within cluster variation, adjusting for strata and individual covariates for example pre-intervention level of RQLQ(S). Estimates and standards errors of the intervention effects will be reported and normal chi-square tests on the ratio of these estimates to their standard errors will be used. An estimate and confidence intervals for the ICC will be calculated, adjusting for baseline RQLQ(S). Analysis will be undertaken using MLwiN.

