### Allocation of trial interventions

The general practice was the unit of allocation. Randomisation to intervention or control was carried out separately within each of the five participating regions: Lothian; Borders; Durham and Tees Valley; Northumberland Tyne and Wear, York. For the four regions with more than two practices, this was done using minimisation based on achieving optimum balance for practice list size (three strata <5000, >5001, but <10000, >10000 patients currently registered) and deprivation score (Index of Multiple Deprivation), according to the methods described by Carter and Hood [18]

The reason for randomisation by centre was to help ensure an even distribution of intervention and control practices as there is likely to be a geographical variation in pollen counts between centres.

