### Secondary outcomes

• Weekly pollen count data collected over the duration of trial.

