#### Study timeline

Trial Start: 1 August 2008

Baseline data collection: March 2009 and 2010

Interventions in general practice: April 2009 and 2010 (training), May/June 2009 and 2010 (patient appointments with HCPs)

End of interventions in general practice: June 2009 and 2010

End of 6 week follow-up: August 2009 and 2010

Start of data analysis: September 2010

Planned study end date: December 2010

Duration: 29 months

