### Current study status

At the time of submission, outcome data has only been obtained for 160 patients from 24 general practices, leading to lower power than was originally intended for the study, and further recruitment is therefore planned in the summer of 2010. It is planned to recruit a further 10 practices, which will achieve the original target of 220 patients if cluster sizes are similar to those for 2009. We calculate that this will give similar power to that originally planned, because the gain in power from having more clusters of smaller size will be counterbalanced by some loss of power from the fact that there was substantial variation in the sizes of the different clusters.

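### The trial will pool two pollen seasons, but neither adjustment set contains year, so any season-wide shift in RQLQ(S) inflates the reported standard error and ICC and costs power.

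*Protocol article*

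**What the plan says.** Under *Current study status*, the protocol article reports outcome data for 160 patients from 24 practices in 2009 and adds: "It is planned to recruit a further 10 practices". *Study timeline* gives two dates for each stage from baseline on, for example "End of 6 week follow-up: August 2009 and 2010".

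Under *Adjusting for*, two covariate sets are numbered. The first is "Practice level stratum (region, list size and IMD or proxy) and baseline RQLQ(S"; the second is the same practice-level set without the baseline score. The paragraph that follows specifies a random-effects model and an ICC estimate with confidence intervals. It leaves some room for further covariates, but only at the individual level.

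Two other places bear on the point. *Allocation of trial interventions* randomises within region because "there is likely to be a geographical variation in pollen counts between centres". *Statistical analysis* says that baseline was collected before the pollen season and that scores at its peak may be high.

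**The concern.** The article treats pollen as a source of variation between practices and handles its geographical part by stratifying and adjusting for region. The second season adds a part that varies by year, and the adjustment sets do not reflect it. As planned, the 2010 practices are additional ones, so year is a practice-level factor: each practice belongs to one season.

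If follow-up scores run higher or lower in one season, a model without year can only attribute the difference to the practice random effect. The pre-season baseline score cannot carry that year's pollen effect. Three things are at stake: the standard error of the primary comparison, the power that the extension was meant to restore, and the ICC that the trial has undertaken to report.

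**Working it through.** **Inputs from the article.** *Sample size*: "using a standard deviation of 1.2 [20] with a power of 80"%, a "minimal clinically important difference of 0.5 in RQLQ(S) score at a significance level of 5"%, ICC 0.02 and clusters of 10. *Current study status*: 24 practices with 160 patients (160/24 = 6.67 per practice), plus 10 practices, 34 in all.

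**Assumptions.** The season shift *d* in mean follow-up RQLQ(S) is not in the document; the range taken is 0 to 1.0 points. The test is two-sided, which reproduces the stated sample size.

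**The article's own figure.** n per arm = 2 × (1.96 + 0.84)² × 1.44 / 0.25 ≈ 90.4, or about 181 in total (stated: 180). The design effect is 1 + 9 × 0.02 = 1.18, and 180 × 1.18 = 212, which rounds up to 22 clusters of 10 = 220. This reproduces. The power of 22 × 10 is about 81%; that of the 2009 data alone (24 × 6.67) is about 70%.

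**Effect of omitting year.** With arms balanced within year, a shift *d* adds p(1 − p)d² to the between-practice variance, where p = 24/34, so p(1 − p) = 0.208. Then

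SE = √{4 × [σ²·ICC + σ²(1 − ICC)/m + 0.208d²] / 34}

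with σ² = 1.44, σ²·ICC = 0.0288 and σ²(1 − ICC)/m = 1.4112/6.67 = 0.2117. Power is for a difference of 0.5.

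| Assumed shift *d* | Added variance | SE | Change in SE | Power | Apparent ICC |
|---|---|---|---|---|---|
| 0, or any *d* with year in the model | 0 | 0.168 | – | 84% | 0.020 |
| 0.25 | 0.013 | 0.173 | +3% | 83% | 0.029 |
| 0.5 | 0.052 | 0.186 | +10% | 77% | 0.054 |
| 0.75 | 0.117 | 0.205 | +22% | 68% | 0.094 |
| 1.0 | 0.208 | 0.230 | +37% | 59% | 0.144 |

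**Unequal clusters.** A REML simulation on the same inputs, with an assumed coefficient of variation of cluster size of 0.6, gives a mean SE of 0.176 with year. Without year it is 0.193 at *d* = 0.5 (+10%; power 75% against 82%) and 0.241 at *d* = 1.0 (+37%). The mean estimated ICC at *d* = 0.5 is about 0.06 without year, against about 0.03 when there is no season shift to absorb.

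**True spread of the estimate.** In simulations with balanced arms, the empirical SD of the effect estimate is nearly the same in both models: 0.173 without year against 0.171 with it at *d* = 0.5, and 0.181 against 0.173 at *d* = 1.0. So the reported SE overstates the real uncertainty and the test is conservative.

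**Unbalanced arms in 2010.** Take 12 practices per arm in 2009, and 3 control and 7 intervention practices in 2010. Omitting year shifts the estimate by d × (7/19 − 3/15) = 0.5 × 0.168 = 0.084 at *d* = 0.5. A true −0.50 is then estimated as about −0.42; simulation gives −0.417, and −0.501 with year in the model.

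**The case against.** The strongest reply concerns size. No place in the article gives a difference between seasons, and at 0.25 points the SE rises by only about 3%. The 37% is the top of an assumed range, and the cluster-size variation of 0.6 is also assumed; the article says only that it was substantial. The illustration also leaves out the planned adjustment for region, list size, deprivation and baseline. All of this stands: the figures show what a given shift would do, not what to expect.

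A second reply is that an article written mid-trial may leave a season term to a fuller plan. That mitigates the point but does not remove it. The two sets are numbered and look fixed, and the open wording covers individual covariates, which year is not under this design.

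A third is that region may already do the work. If all the 2010 practices come from new regions, year is aliased with region and the extra term adds nothing. The article does not say where they will come from.

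A reader might infer more than the document supports in three ways:

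- That the effect estimate itself becomes much less precise. With arms balanced within year its true spread barely changes; the reported SE and the power suffer.
- That bias is established. It needs imbalance by arm within year, and the article does not report how the 2010 practices fall by arm. Its stated method of allocating within region would tend to limit imbalance.
- That listing "Weekly pollen count data collected over the duration of trial" under *Secondary outcomes* contributes to the problem. Training cannot change pollen, so the counts are a descriptive exposure measure. But the label inflates no variance, and the abstract and aims do not name pollen as an outcome. This is at most a wording note.

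**Conclusion.** The point holds for the missing year term. Two seasons will be pooled, neither adjustment set contains year, and the pre-season baseline cannot stand in for it. With arms balanced within year the harm is an overstated SE and ICC with lost power: small at a shift of 0.25 points, and material from about 0.5. At 0.5, power of about 75% would undercut the statement under *Current study status* that the extension gives similar power to the original design; that statement considers only the number and size of clusters. Bias is a conditional further risk. These sizes rest on the assumed shift, ICC 0.02, SD 1.2, 34 practices averaging 6.67 patients and, for the REML figures, the assumed variation in cluster size. The omission should be corrected, but it does not invalidate the comparison.

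**What to change.** Add year of participation (2009 or 2010) as a fixed effect in both models under *Adjusting for*, and record the change before analysis starts in September 2010. The cost is one practice-level degree of freedom and about 1% or less in SE if the seasons do not differ. No extra data are needed, because year is known for every practice. If all the 2010 practices come from regions not used in 2009, state that region already carries the season difference. Optionally, describe the pollen counts as an exposure measure and not as an outcome.

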**Methods/Design:**

Adolescents with a history of hayfever registered in general practices in Scotland and England were invited to participate in a cluster randomised controlled trial. The unit of randomisation is general practices.

The educational intervention for healthcare professionals consists of a short standardised educational course, which focuses on the management of allergic rhinitis. Patients in the intervention arm of this cluster randomised controlled trial will have a clinic appointment with their healthcare professional who has attended the training course. Patients in the control arm will have a clinic appointment with their healthcare professional and will receive usual care.

The primary outcome measure is the change in the Rhinoconjunctivitis Quality of Life Questionnaire with Standardised Activities (RQLQ(S)) score between baseline and six weeks post-intervention in the patient intervention and control groups.

Secondary outcome measures relate to healthcare professionals' understanding and confidence in managing allergic rhinitis, changes in clinical practice, numbers of consultations for hayfever and adolescent exam performance.

A minimum of 11 practices in each arm of the trial (10 patients per cluster) will provide at least 80% power to demonstrate a minimal clinically important difference of 0.5 in RQLQ(S) score at a significance level of 5% based on an Intraclass Correlation Coefficient (ICC) of 0.02.

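### The primary analysis fixes a large-sample Wald test for an effect estimated from 24–34 practices without naming the estimation method, and the 80% power claim for 22 practices ignores cluster-level degrees of freedom

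*Protocol article*

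**What the plan says.** Under Statistical analysis (Comparison between treatment arms, Adjusting for), the protocol article specifies a multilevel random-effects model. It adjusts for region, list size, deprivation and, in the first of two versions, baseline RQLQ(S). For inference, "normal chi-square tests on the ratio of these estimates to their standard errors will be used". On software it says "Analysis will be undertaken using MLwiN". It does not state the estimation method or any small-sample correction.

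Under Sample size, the calculation is made "using a standard deviation of 1.2". It aims at 80% power for a 0.5-point difference, testing at the 5% level, with clusters of 10 and the ICC set to 0.02. The result is that the trial "required a total of 22 clusters and an adjusted sample size of 220 patients (unadjusted 180"). The Abstract turns this into a floor: "A minimum of 11 practices in each arm of the trial (10 patients per cluster) will provide at least 80% power".

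Under Current study status, 24 practices have supplied outcome data on 160 patients. Ten more practices are planned, to reach 220 patients with power similar to that first intended. That section weighs the gain from more, smaller clusters against the loss from unequal cluster sizes.

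**The concern.** Practices are randomised, so the precision of the arm effect depends on a between-practice variance estimated from few units. A normal or chi-square reference treats that variance as known. Two things can go wrong.

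- Maximum likelihood does not allow for the degrees of freedom spent on fixed effects. The between-practice variance is then biased towards zero and is sometimes estimated as exactly zero, which removes the allowance for clustering.
- Even with an unbiased variance, the normal critical value of 1.96 is smaller than the t value that 15–25 practice-level degrees of freedom call for.

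The stake is the primary outcome. If the test is liberal, p-values are too small and intervals too narrow, which favours a false claim of benefit. The sample size rests on the same normal reference, so its power figure may be optimistic.

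**Working it through.** **Inputs from the protocol article.** Difference 0.5, SD 1.2, significance level 5% (two-sided assumed; this reproduces the stated size), cluster size 10, ICC 0.02, 22 clusters (Sample size). Five regions and three list-size strata (Allocation of trial interventions). 24 practices with 160 patients, then 10 more practices to reach 220 patients (Current study status).

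**1. Reproduce the stated size.** n per arm = 2 × (1.96 + 0.8416)² × 1.2² / 0.5² = 90.4, rounded up to 91, so 182 in total (stated: 180). Design effect = 1 + (10 − 1) × 0.02 = 1.18. 182 × 1.18 = 214.8 patients, or 21.5 clusters, rounded up to 22 clusters and 220 patients. The plan's figure is reproduced, with normal quantiles.

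**2. Degrees of freedom.** Practice-level parameters: intercept 1, arm 1, region 4, list size 2, deprivation 1 (assumed to be one linear term), total 9. Remaining: 22 − 9 = 13, 24 − 9 = 15, 34 − 9 = 25. Counting only intercept and arm: 20, 22 and 32.

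**3. Power of 22 × 10 at ICC 0.02.** SE = 1.2 × √(4 × 1.18 / 220) = 0.176; noncentrality = 0.5 / 0.176 = 2.84.

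- Normal reference: 81.2%
- t, 20 df (critical value 2.086): 77.2%
- t, 13 df (critical value 2.160): 74.9%

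With practices − 2 df, 24 clusters of 10 are needed for 80% (81.0% on 22 df).

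**4. Power of the extended design, 34 practices and 220 patients, ICC 0.02.** Mean cluster size m = 220 / 34 = 6.47. Design effect = 1 + [(1 + CV²) × m − 1] × ICC. The article calls the variation in cluster size substantial but gives no coefficient of variation (CV), so a range is assumed.

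| CV | Design effect | t, 32 df | t, 25 df |
|---|---|---|---|
| 0 | 1.109 | 81.2% | 80.5% |
| 0.5 | 1.142 | 80.1% | 79.4% |
| 0.7 | 1.173 | 79.0% | 78.3% |

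**5. Type I error of the Wald z test.** The random-intercept model was simulated under no effect, with 4,000 replicates per setting (Monte Carlo standard error about √(0.05 × 0.95 / 4000) = 0.3 points). Practice covariates were included and a cluster-size CV of 0.6 assumed. Maximum likelihood (ML) was run in two independent sets; the restricted likelihood (REML) figures are from the second set.

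| Fit | ICC | 24 practices | 34 practices |
|---|---|---|---|
| ML | 0.02 | 7.3%, 7.7% | 8.1%, 7.0% |
| ML | 0.05 | 9.3%, 10.0% | 8.7%, 8.7% |
| REML | 0.02 | 5.1% | 4.7% |
| REML | 0.05 | 6.0% | 5.7% |

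The first set gave 4.8–5.7% for REML with z, rising to 6.4–6.7% at ICC 0.10. A further run gave about 6–7% (ICC 0.02) and 10% (ICC 0.05) under ML, and about 4.5–5% and 6% under REML.

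**The case against.** The strongest reply is that the estimator is a detail an article may leave to a fuller plan, and that the stated test fitted by restricted likelihood holds roughly 5% at the planning ICC. This stands. A reader might infer that the 5% error rate fails outright; the document does not support that, because the excess arises mainly under maximum likelihood, which it never specifies. What remains is that the one element it does fix, the normal reference, is the liberal one, and that error control then rests on an option left open.

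A reader might also infer that the power calculation ignores the number of clusters. It does not. A design effect is applied, Table 1 gives cluster counts for three ICCs, and Current study status weighs cluster number against size. Only the cluster-level degrees of freedom are left out.

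Nor do both harms occur together. Keeping the normal reference keeps the nominal 81% power and puts the error rate at risk; moving to t protects the error rate and costs power.

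On power, three replies deserve weight.

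- Baseline adjustment is planned but not credited. If 1.2 is the SD of the follow-up score, a baseline correlation of 0.25–0.30 would bring 22 × 10 to about 80–81% on 20 df, or 78–79% on 13 df. The article gives no correlation and does not say which SD 1.2 is, so this is possible but not established.
- The 22-practice design has been overtaken. At 34 practices and 220 patients the shortfall is at most about two points. At the present 24 practices and 160 patients, power with equal cluster sizes is about 65–67% by t, but only 70.5% even by z, so most of that loss comes from missing patients, which the article acknowledges.
- Recruitment was "inflated by 20% to account for possible losses to follow-up". That allowance is meant to be used up by losses and adds no practices. Losses so far are (230 − 160) / 230 = 30%.

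The simulations are also somewhat pessimistic. In the second set, the covariates carry no information, and list size and deprivation are assigned at random, whereas the trial minimises on both in four of its five regions.

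**Conclusion.** The point holds in a limited form. The plan fixes a large-sample reference for a practice-level effect with about 15–25 practice-level degrees of freedom and leaves the estimator open. Depending on that choice, the type I error is about 6–8% (ICC 0.02) to 9–10% (ICC 0.05) under maximum likelihood, or about 5–6% under restricted likelihood. These figures rest on assumed cluster-size variation.

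The Abstract's power claim for 11 practices per arm holds only with normal quantiles. On the protocol's own inputs and a t reference it is about 77% (20 df) or 75% (13 df), without baseline adjustment. The extended design is borderline at about 78–81%, over assumed CVs of 0 to 0.7. It should be changed before the analysis, which the timeline starts in September 2010, but it does not undermine the design.

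**What to change.** State that the model will be fitted by restricted likelihood (RIGLS or REML). Test the arm effect against a t distribution with small-sample degrees of freedom (Satterthwaite, Kenward-Roger, or practices minus practice-level parameters), with confidence intervals on the same basis. Restate the power of 22 practices × 10 patients as about 77% without baseline adjustment, and that of 34 practices with 220 patients as about 78–81%. If credit is taken for baseline adjustment, give the assumed correlation and say which SD the 1.2 refers to.

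The cost is slightly wider intervals and possibly a second package for the degrees of freedom. No further data are needed.
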